### ‘Treatment as usual’ (control) group

For the purposes of the feasibility evaluation, the inclusion of a control group (ie, TAU) is important because it allows for a more realistic evaluation of the operational aspects (ie, recruitment, retention and randomisation) as well as the implementation of the intervention.^23^ If conducted in an unblinded, non-randomised manner, the outcomes, particularly for a complex psychosocial intervention such as is being tested here, may be quite different. Furthermore, since previous evidence enabled us to power the primary outcome measure, cognitive function, for an evaluation of efficacy, a pilot trial was considered possible and this required inclusion of a control group to account for the natural progression of symptoms during the trial. Specifically, in the TAU comparator arm, dyads will not receive any additional intervention to their standard NHS treatment for PD and cognitive impairment or DLB. Typically, this involves dopamine replacement therapy for the symptomatic relief of Parkinsonism, cognitive enhancing medication (eg, cholinesterase inhibitors) and support from a Parkinson's disease nurse specialist. Since people with Parkinson's-related dementia tend to have significant symptoms in multiple domains, the support of occupational therapist, speech and language therapists and physiotherapists is often required. These interventions will be available to both the TAU as well as those dyads randomised to the active treatment arm. Treatment fidelity will be actively monitored in the control group, as it is in the experimental group, to ensure that the control group do not receive an active intervention component which could reduce the effect size between the experimental and control groups or, similarly, to ensure that an iatrogenic component is not added to the control group which could artificially inflate the difference in outcomes between the two groups.^24^

### Patient and public involvement

Service users, service providers and PPI representatives have been involved in the developmental stages leading up to this study. To ensure that PPI continues to be integrated throughout the INVEST trial, two couples (both involving a person living with PD and their life partner) are active members of the Trial Steering Group (TSG). Additional PPI representatives will be involved in the piloting of interview schedules, advising on the language used to raise awareness of the study, promoting the study through networks and disseminating the research.

### Outcome measures

#### Feasibility and acceptability measures

We shall describe individual demographic and clinical characteristics of participants and companions. We will evaluate several feasibility and acceptability components with a series of outcome measures outlined in table 4. The recruitment and attrition rates to inform subsequent trials will be estimated.

**Table 4 T4:** Description of feasibility measures

Feasibility component	Measure	Described as
Recruitment	Recruitment rate	The number of dyads consented/number eligible
Attrition	Attrition rate	The number of dyads withdrawn/number consented
Therapy adherence	Therapy log (companion's diary)	The total dose (frequency and duration) of the intervention delivered, recorded by the companion after each session
Acceptability of therapy	Therapy log (companion's diary)	Companions will rate the extent to which (in each session) the participant was interested, motivated, gained a sense of achievement; took the initiative and displayed emotional responses. Ratings will be made on a 5-point Likert scale on which ‘1’= strongly disagree and ‘5’=strongly agree.
Acceptability of assessments	Interview record form/focus group	Mixed methods. Quantitative data will include response rates, time taken and level of missing data. Qualitative investigation (assessors interview record form/focus group with blinded assessor) will explore the process: how were the assessments administered, queries raised by respondents, respondents’ markings on the instrument, practical difficulties observed and strategies employed to overcome challenges.

To triangulate the data, qualitative semistructured interviews will be conducted with a small sample following completion of the intervention. The interviews will seek to ascertain acceptability information relating to expectations and experiences of the therapy and barriers and facilitators to completing the therapy. Data will be collected from a purposive sample of 12 dyads, since new themes are reported to occur infrequently beyond this sample size.^25^ The purposive subsample will aim to maximise diversity in dyads’ characteristics to increase the validity and transferability of research findings to other settings. The sample will include (1) people taking part in the therapy, (2) men and women, (3) people of ages crossing the age range of the main sample and (4) people with different levels of cognitive ability (eg, PDD and MCI-PD). Approximately three to four dyads will be invited for interview from each centre.

All audio-recorded interview data will be transcribed verbatim and analysed using thematic analysis or other appropriate analytical processes.

#### Primary and exploratory outcome measures

The piloted efficacy and exploratory outcome measures for the participant are outlined in table 5a and the exploratory outcome measures for the companion in table 5b. The pilot efficacy measure on which the study has been powered is cognitive function as assessed using the Addenbrooke's Cognitive Examination III^26^ and the Everyday Cognition Questionnaire.^27^ Although the pilot trial has been powered on a previously reported effect size, the adaptation of the therapy and single outcome measure means that any potential treatment effects will be interpreted cautiously in order to not mislead the subsequent sample size and power calculation of the full RCT with multiple outcomes.^28^ With this caveat, we will test the hypothesis that compared with the TAU group, the difference in the total cognitive score between baseline and endpoint will be significantly greater in the experimental group. We will undertake a complete case analysis, only including trial completers without missing data, as well as an additional analysis based on last observation carried forward for dyads with missing data. Group differences in the change of outcome measures will be assessed using t-test or analysis of covariance adjusting for baseline differences, including cognitive stage at baseline.

**Table 5 T5:** Primary and exploratory outcome measures

Measure/author	Purpose	Time point

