## Methods

This protocol was prepared in accordance with SPIRIT 2013 statement^12^ (checklist is available as an online supplementary file). The trial is registered with the ISRCNT (ISRCTN11455062); all study-related items from the WHO Trial Registration Data Set are available at the registry. The protocol lies within a research programme comprising a series of sequential steps in the development, feasibility testing, piloting and eventual full-scale trialling of a complex psychosocial intervention for people with PDD, MCI-PD or DLB. The programme has followed the UK's MRC's updated Guidance on ‘Developing and Evaluating Complex Interventions^10^ and is now at the feasibility, exploratory and pilot trial stage, which we describe here. Specifically, this part of the programme is a fully controlled randomised single-blind exploratory pilot trial with an embedded feasibility process evaluation and evaluation of new outcomes. The protocol for the process evaluation is not reported here but will form the basis of other papers. The pilot trial is designed and powered to test the hypothesis that CST-PD is superior to TAU for people with PDD, MCI-PD or DLB in improving cognitive function when assessed at baseline and 12 weeks post-randomisation. The therapy will be delivered in participants’ homes with recruiting sites in locations in Greater Manchester and other regions in the UK. A CONSORT-style flow chart for the trial is shown in figure 1.

10.1136/bmjopen-2017-016801.supp1Supplementary material 1

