### Randomisation and blinding

Eligible dyads will be identified at recruiting centres by trial collaborators (principal investigators) and research nurses and therapists. Participant and companion information sheets outlining the study objectives, risks and benefits will be shared with each dyad. Informed consent from the participant and companion, based on the Good Clinical Practices guidelines published by International Council for Harmonisation,^20^ will be gained during the home screening visit (participant and companion information sheets and informed consent forms are available as on online supplementary file). In line with the aforementioned iCST/CST trials, guidance from the British Psychological Society on evaluation of capacity will be followed. In the event of a participant with PDD/DLB not having capacity at study entry or losing capacity after study entry, the ethics committee has approved the INVEST trial implementer to gain consent from an acceptable, nominated representative. During the home screening, the unblinded trial implementer will administer the Montreal Cognitive Assessment (MoCA)^21^ and Schwab and England Activities of Daily Living Scale^22^ to confirm eligibility and collect demographic data. Once the participant and companion are consented, blinded assessors will conduct baseline assessments in the dyad's home.

Following baseline assessment, the unblinded trial implementer will randomise the dyad to one of two arms: CST-PD or TAU. A tamper proof process of single-strata, blocked randomisation will be applied and communicated via telephone and confirmatory email by an independent arbiter, the Manchester Academic Health Science Centre Clinical Trials Unit. Due to the nature of the intervention, dyads will not be blind to treatment allocation.

Immediately following the intervention period (see below for details), the blinded assessors will visit dyads in their home to conduct post-test assessments. The unblind trial implementer will remind all dyads to maintain the blind during the assessment. Following assessment, blinded assessors will be asked to record the arm to which they believed the dyad was allocated to.

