### Active intervention

The active intervention, CST-PD, is based on conventional CST^7^ and iCST^5^ and was developed by means of an iterative process involving significant user, companion and professional input. This adaptation process is described in detail elsewhere and has resulted in a condition-specific cognitive stimulation therapy manual with training guidance. The manual comprises over 60 topics categorised into nine different themes (table 3). Each topic contains several cognitively stimulating activities, for example, discussion suggestions, word association and creative tasks. Activities vary in complexity and can be matched and adapted to suit the needs of the participant. It is recommended that the companion-guided therapy is delivered in 30 min sessions, three times a week over 10 weeks.

**Table 3 T3:** Themes and sample topics from the CST-PD manual

Session theme	Sample topics
Personal life	Childhood, family, relationships
Food	World cuisine, staying healthy, ingredients
Hobbies and leisure	My perfect day, pets, gardening
Art	History of art, Lowry and Turner, architecture
Media and entertainment	Musical instruments, current affairs, technology
Nature	Weather, water, animal kingdom
Seasons	Spring, Summer, Autumn, Winter
Travel and culture	Continents, flags, Blackpool
Games and tasks	Board game, proverbs, colouring and doodling

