**a) Efficacy and exploratory outcome measures for the participant**		
The Addenbrooke's Cognitive Examination III^26^	Assesses cognitive function	Baseline/post-test
Everyday Cognition Questionnaire^27^	Measures everyday cognition in people with movement disorders	Baseline/post-test
Pill Questionnaire^37^	Measures functional capacity	Baseline/post-test
Lille Apathy Rating Scale^38^	A scale to detect and quantify apathy	Baseline/post-test
Relationship Satisfaction Scale^39^	Assesses level of satisfaction in a relationship	Baseline/post-test
The Brief Resilience Scale^40^	Assesses the ability to recover from stress	Baseline/post-test
Interpersonal Reactivity Index^41^	Measures empathetic concern	Baseline/post-test
Hospital Anxiety and Depression Scale^42^	Assesses depression and anxiety	Baseline/post-test
Parkinson's Disease Questionnaire-39^43^	A Parkinson's disease-specific quality of life measure	Baseline/post-test
Dementia Cognitive Fluctuation Scale^44^	Assesses proxy-reported fluctuations in cognition	Baseline/post-test
The Neuropsychiatric Inventory^45^	Assesses presence or absence of behavioural disturbances	Baseline/post-test
EuroQoL 5D^31^	Used for calculation of quality-adjusted life-years	Baseline/post-test
Client Services Receipt Inventory^30^	Collects information about medications and services used before entering the trial and during the trial	Baseline/post-test

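### The efficacy measure pairs an assessor-administered test with a questionnaire most likely answered by an unblinded dyad member, and gives neither priority, so reporting bias can enter the efficacy test

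*Protocol article*

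**What the plan says.** Under Primary and exploratory outcome measures, the protocol article states: "The pilot efficacy measure on which the study has been powered is cognitive function as assessed using" the Addenbrooke's Cognitive Examination III, and then adds the Everyday Cognition Questionnaire. The hypothesis in the same paragraph is that "the difference in the total cognitive score between baseline and endpoint will be significantly greater in the experimental group". The article does not say how the two instruments make up that score, or which one decides.

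Table 5a lists the questionnaire with the purpose "Measures everyday cognition in people with movement disorders" and does not say who completes it.

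On blinding, the Methods section describes "a fully controlled randomised single-blind exploratory pilot trial". Under Randomisation and blinding, "the blinded assessors will visit dyads in their home to conduct post-test assessments", but "Due to the nature of the intervention, dyads will not be blind to treatment allocation". Dyads are reminded to maintain the blind, and assessors record which arm they believe the dyad was in. Under Data management, the statistician works on data coded by arm.

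On delivery, the Active intervention section says "It is recommended that the companion-guided therapy is delivered in 30 min sessions, three times a week over 10 weeks". The companion is trained, receives information on the therapy's objectives and is contacted weekly. TAU dyads receive nothing beyond standard NHS care.

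**The concern.** A blinded assessor protects a measure when the assessor's own administration and scoring produce the result. The Addenbrooke's examination is of that kind. A questionnaire on everyday cognition depends on what someone has seen in daily life, and the assessor meets the dyad only at assessment visits. The answers therefore most likely come from the participant or the companion, both of whom know the allocation.

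The protocol's other safeguards (the reminder, the assessor's guess, the masked statistician) act on the assessor or the analyst. None of them acts on what an unblinded respondent reports.

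At stake is the single superiority test, together with the estimate of effect and variance that is meant to inform a definitive trial. If expectation shifts the questionnaire answers in one arm, part of any difference found could reflect reporting and not cognition.

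**Working it through.** **Inputs from the protocol (Sample size).** 27 completers per group, correlation 0.5 between baseline and endpoint, standardised effect 0.4, 80% power, 15% attrition. The t-test and ANCOVA come from Primary and exploratory outcome measures.

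**Assumptions, not in the protocol.** Two-sided 5%. No true effect. A reporting shift b of 0.2, 0.3 or 0.4 SD towards CST-PD, on the questionnaire only. Correlation r between the instruments of 0.3 to 0.5. An equally weighted average of standardised scores as one possible form of the total score.

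**Step 1: the plan's own figure.** A repeated-measures group-by-time interaction with f = 0.4/2 = 0.2, correlation 0.5 and two-sided 5% needs 52 in total, or 26 per group. At 27 per group its power is 82%. Enrolment of 27/0.85 = 31.8 rounds up to 32, as stated. A direct two-group comparison of 0.4 SD would need 99 per group (change score) or 74 (ANCOVA). That gap is a separate matter. Here 27 per arm is taken as given.

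**Step 2: outcome SD, in baseline SD units.**
- Change score: sqrt(2(1 - 0.5)) = 1.
- ANCOVA: sqrt(1 - 0.5^2) = 0.866.

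**Step 3: standard error of the group difference.** SD x sqrt(2/27) gives 0.272 for the change score and 0.236 for ANCOVA.

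**Step 4: questionnaire tested alone.** The non-centrality is b/SE. The rejection rate comes from the non-central t distribution, with 52 degrees of freedom (change score) or 51 (ANCOVA).

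| Shift b | Change score: b/SE, rate | ANCOVA: b/SE, rate |
|---|---|---|
| 0.2 | 0.73, 11% | 0.85, 13% |
| 0.3 | 1.10, 19% | 1.27, 24% |
| 0.4 | 1.47, 30% | 1.70, 38% |

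**Step 5: equally weighted composite.** Averaging halves the shift, and the average has SD sqrt((2 + 2r)/4). The shift in composite SD units is therefore (b/2)/sqrt((1 + r)/2).

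| b | r | Composite shift | Change score | ANCOVA |
|---|---|---|---|---|
| 0.2 | 0.3 | 0.124 | 7% | 8% |
| 0.2 | 0.5 | 0.115 | 7% | 8% |
| 0.4 | 0.3 | 0.248 | 15% | 18% |
| 0.4 | 0.5 | 0.231 | 13% | 16% |

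For comparison, the nominal rate is 5% and the effect used for planning is 0.4 SD.

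**The case against.** The strongest objection is that the respondent is not stated. Table 5a labels the Dementia Cognitive Fluctuation Scale as proxy-reported and gives the Everyday Cognition Questionnaire no such label. A reader might infer that companions certainly rate the success of a therapy they delivered themselves. The protocol does not say so. Reporting by a dyad member is a strong inference, and the companion mechanism holds only if the companion answers. If the instrument turned out to be scored by the assessor on performance, the point would fall.

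Three other strong readings also go too far:
- One might say that half of the measure is unprotected. No weighting is given, so that is true only as a count of instruments.
- One might say that the single-blind label is false. It is not: the protocol states openly that dyads know their allocation, and open allocation cannot be avoided here.
- One might say that the bias is shown to favour CST-PD. Direction and size are assumed; trained companions might notice more deficits. The rates above show sensitivity to a shift and are not evidence of one.

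It is also fair that efficacy is a secondary, exploratory objective, that caution in interpretation is promised, and that piloting an everyday-function measure suits a feasibility study. But the caution is attributed to the adaptation of the therapy and to the single outcome measure, not to unblinded reporting. The Methods section also says the trial is designed and powered to test superiority. Piloting the questionnaire does not require it to sit inside that test.

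**Conclusion.** The point holds in a limited form. The protocol places a questionnaire, most likely answered by someone who knows the allocation, in the efficacy measure beside an assessor-administered test. It gives the test no priority and does not name this source of bias. Assessor blinding does not remove it.

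Under the stated assumptions, a shift of 0.2 to 0.4 SD raises a 5% error rate to between 11% and 38% if the questionnaire is tested alone, and to about 7-18% in an equally weighted composite, across the two analyses that the protocol allows. These ranges rest on an assumed shift, an assumed composite and an unnamed respondent. They do not show that this trial's result will be biased. The change is worth making, but the flaw does not invalidate a trial whose main purpose is feasibility.

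**What to change.** Test the efficacy hypothesis on the assessor-administered Addenbrooke's Cognitive Examination III alone, which also fits the protocol's own reference to a single primary outcome. Move the Everyday Cognition Questionnaire to the exploratory outcomes. Name its respondent and, if that is a dyad member, identify the measure as unblinded when it is reported.

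The cost is one measure fewer behind the efficacy test, and the everyday-function aspect of cognition no longer contributes to it. Recruitment opened on 1 March 2016, so the change needs a protocol amendment with ethical approval and the notifications listed under Ethics and dissemination. Both instruments are still collected at both visits, so no data are lost.

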### Research questions and hypotheses

The following are research questions for the feasibility and exploratory study:Is it possible to recruit sufficient dyads in a timely manner?What is the acceptability and tolerability of the intervention by dyads?Which are the most clinically meaningful and acceptable outcomes by which to assess efficacy?Based on the findings, what would the sample size of a fully powered definitive RCT of the intervention be?

The following is the hypothesis to explore potential efficacy of the intervention:In people with PDD, MCI-PD or DLB, the change in cognitive function from baseline to withdrawal of CST-PD at 12 weeks will favour the intervention compared with treatment as usual (TAU).

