### Sample size

A predetermined sample size for the feasibility aspects of this study is not required, since inferential statistics will only be exploratory. The sample size is determined by that required to detect a clinical meaningful difference in our primary outcome measure, cognitive function. To determine sample size, we referred to the previous literature^7 8 16^ and, taking a conservative approach, have estimated the standardised effect size on cognition of the parent form of the intervention to be 0.4. Thus, assuming 80% power and a correlation coefficient of 0.5 between baseline and endpoint on cognitive outcomes, the required sample size is 27 completers per group. By enrolling 32 dyads per group, it will allow for a 15% attrition rate (consistent with pilot sample guidance^17^). For the secondary, exploratory outcomes, the proposed sample size of 27 per group is within the recommended guidelines (24–50 participants^18 19^) required to estimate the standard deviation (SD) for a sample size calculation.

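### With a single post-test, last observation carried forward can only insert the baseline score, so it assumes no change in dropouts and is a weak check on missing data

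*Protocol article*

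**What the plan says.** The section on primary and exploratory outcome measures sets out two ways of handling missing outcomes, one of complete cases and one with carried-forward values: "only including trial completers without missing data, as well as an additional analysis based on last observation carried forward for dyads with missing data". Groups are then compared by t-test on change or by ANCOVA.

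The Methods section says the efficacy hypothesis concerns cognition "when assessed at baseline and 12 weeks post-randomisation". Table 5 gives the same schedule, "Baseline/post-test", for both cognitive instruments and for every other measure. The MoCA is given at the screening visit to confirm eligibility. The weekly contacts in the intervention arm cover consent, adherence and support. No cognitive score is collected between baseline and post-test.

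The section on the control arm justifies that arm as "a control group to account for the natural progression of symptoms during the trial". On dropout, the Sample size section says: "By enrolling 32 dyads per group, it will allow for a 15% attrition rate".

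**The concern.** Carrying the last observation forward has a meaning of its own only when there are intermediate visits. Here the last observation before a missing post-test is always the baseline, so the method is baseline carried forward. Each affected dyad enters the analysis with a change of exactly zero, treated as if it had been measured. This conflicts with the protocol's own expectation that symptoms progress during the trial.

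The analysis is also the only check on missing data that the protocol names beside the complete case analysis. A useful check makes a different and defensible assumption about the dyads who were lost. This one makes an assumption that the protocol itself contradicts. It can move the estimate either way: towards zero if the arms lose equal shares, and towards CST-PD if that arm loses more. Heavier loss in CST-PD is plausible, because the withdrawal rule under Active intervention is triggered by a run of weeks without therapy, and only CST-PD dyads have study therapy to miss.

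**Working it through.** **Inputs from the protocol (Sample size).** 27 completers and 32 enrolled per group; 15% attrition; effect 0.4 SD; baseline-endpoint correlation r = 0.5.

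**Assumptions.** Score SD is 1 at both time points. The rate of decline and the split of dropout between arms are not given, so ranges are shown. Alpha is not stated; 0.05 two-sided is used.

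**Plan's own figure.** 27 / (1 − 0.15) = 31.8, so 32 per group, as stated. The share to be filled in is 32 × 0.15 = 4.8, about 5 dyads per arm.

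**Equal dropout, unrelated to outcome.** Let q be the missing share and μ the mean change.
- Expected group difference = (1 − q) × true difference.
- Variance of change = (1 − q) × 2(1 − r) + q(1 − q)μ². With r = 0.5 the full-data variance is 1.
- Baseline-endpoint correlation (μ = 0) = (1 − q)r + q.

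| q | Difference when truth is 0.4 | SD of change (μ = 0) |
|---|---|---|
| 5% | 0.38 | 0.975 |
| 15% | 0.34 | 0.922 |
| 30% | 0.28 | 0.837 |

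At q = 15% and μ = −0.2 the SD of change is 0.925, so the result hardly depends on the decline. The correlation becomes 0.85 × 0.5 + 0.15 = 0.575, and the ANCOVA residual SD falls from √(1 − 0.5²) = 0.866 to √(1 − 0.575²) = 0.818. The SD of the post-test score itself stays at 1.00.

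**Unequal dropout, unrelated to outcome, no true effect.** Spurious difference in favour of CST-PD = (q in CST-PD − q in TAU) × mean decline.
- 25% against 5%, decline 0.2 SD: 0.20 × 0.2 = +0.04 SD.
- Declines of 0.1 and 0.3 SD: +0.02 and +0.06 SD.
- With the split reversed the sign reverses; with equal dropout the difference is 0.

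The complete case difference is about 0 in all of these.

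**Unequal dropout that depends on outcome, no true effect.** This was simulated with 32 per arm, r = 0.5, 25% against 5% missing, declines of 0.2 and 0.4 SD, and logistic dropout with slope 0.5 to 2 per SD of change (4,000 trials per scenario). The carried-forward analysis was biased by +0.10 to +0.25 SD and the complete case analysis by +0.09 to +0.24 SD. The two err together and by similar amounts.

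**Consequence for planning, if carried-forward data were used.** At a difference of 0.4 an ordinary two-arm comparison with 80% power needs 99 per group on change, or 74 by ANCOVA. (How the protocol reaches 27 is a separate question on which nothing here depends.)
- Carried-forward SD with the difference kept at 0.4: 84 or 66 per group.
- Carried-forward SD and carried-forward difference (0.34, or 0.34 / 0.922 = 0.37 standardised): 116 or 91 per group.

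**The case against.** Four points can be made for the plan.

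- **It is only an additional analysis.** The complete case analysis comes first, efficacy is a secondary objective, and attrition and levels of missing data are themselves reported as feasibility outcomes. This stands, and it limits the weight of the point.
- **It does not spoil the definitive trial's sample size.** A reader might infer that the artificial zeros understate the SD and make the later trial about 15% too small (84 instead of 99). The documents do not support that. The size of that trial is a stated question ("what would the sample size of a fully powered definitive RCT of the intervention be"), but nothing says that carried-forward data will answer it. The Sample size section links SD estimation to 27 per group, the completer number, and to the secondary outcomes. The protocol also promises cautious interpretation so as not to mislead later planning. The raw-score SD does not shrink, and if effect and SD both came from the filled-in data the required number would rise.
- **Most of the bias under outcome-related dropout is not due to this method.** A reader might take false-positive rates of 7–22% in the simulated scenarios as its cost. They come mainly from the assumed mechanism and the assumed 25%/5% split: ANCOVA on observed post-tests was also biased, by 0.12 to 0.19 SD, in a similar simulation. Dropping the method would not remove this.
- **Detail belongs in an analysis plan.** That is true of imputation models, but the method is named here and cannot work as intended with this visit schedule.

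**Conclusion.** The point holds in a limited form. That the method amounts to inserting the baseline score follows directly from the visit schedule, and the zero change conflicts with the progression the protocol expects. At 15% equal dropout unrelated to outcome, a 0.4 SD effect becomes 0.34 and the SD of change about 0.92. With heavier loss in CST-PD the method favours that arm by a small amount, +0.04 SD in the illustrated case; this rests on an assumed split and decline. Agreement between the two planned analyses is no evidence against bias from unequal, outcome-related dropout. The main complete case result is untouched by this analysis. This is therefore a modest improvement to a secondary analysis, not an error in the primary one.

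**What to change.** - Drop the carried-forward analysis.
- Analyse all randomised dyads that have a post-test cognitive score, whatever therapy they completed, by ANCOVA of that score on arm, baseline score and cognitive stage. This concerns who is analysed; it makes no proposal about the withdrawal rule.
- As sensitivity analyses, use multiple imputation from the baseline measures already collected, and a version that imputes missing CST-PD outcomes from the TAU distribution. Neither removes bias from outcome-related dropout, but each states a definite assumption and shows how far the result moves under it.
- State that the SD and effect used to plan the definitive trial come from observed data. This is a precaution, since nothing in the protocol says otherwise.

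The cost is a change of wording and a little more analysis work, with slightly wider intervals. No new data are needed.

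### The efficacy test is left as a t-test or an ANCOVA with no rule for choosing, and the baseline cognitive score is not clearly in the model

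*Protocol article*

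**What the plan says.** The protocol article, under Primary and exploratory outcome measures, sets the efficacy hypothesis as a comparison of change: "the difference in the total cognitive score between baseline and endpoint will be significantly greater in the experimental group". The same paragraph ends by saying that group differences in change will be "assessed using t-test or analysis of covariance adjusting for baseline differences, including cognitive stage at baseline". Cognitive stage is the only covariate named, and it belongs to the ANCOVA option. Nothing says which test is primary or what decides between them.

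The Sample size section relies on the link between the baseline and final scores, "a correlation coefficient of 0.5 between baseline and endpoint on cognitive outcomes", but the analysis sentence does not commit to a method that uses it.

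Other sections bear on how much this matters:
- The opening of Methods describes the pilot as designed and powered for a superiority test on cognition.
- Objectives places efficacy among the secondary objectives.
- Sample size calls inferential statistics exploratory.
- Data management has an independent statistician work on coded arms until the primary analysis is finished.

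**The concern.** A t-test on change and an ANCOVA are different tests of one hypothesis. They have different standard errors and can fall on opposite sides of the significance threshold in the same data. With no rule for choosing, a reader of the results cannot tell whether the reported test was chosen before or after the data were seen.

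Two things are at stake. One is precision: the baseline score is collected anyway, and a t-test on change uses it less efficiently than ANCOVA does. The other is the error rate, if the choice were guided by the p-values. The trial is also meant to supply an effect estimate and its variance for planning a definitive trial, and both depend on the model used.

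**Working it through.** **Inputs.** Standardised effect 0.4, correlation r = 0.5, 80% power and 27 completers per group, all from Sample size ("have estimated the standardised effect size on cognition of the parent form of the intervention to be 0.4"; "the required sample size is 27 completers per group"). The article states neither significance level nor sidedness, so two-sided 5% is assumed throughout.

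**The plan's own figure.** The attrition step reproduces: 27/0.85 = 31.8, so 32 per group. The figure of 27 does not follow from a two-arm comparison at 0.4. With n = 2v(1.960 + 0.842)²/0.4², where v is the variance factor derived below, n is 99 per group for a t-test on change and 74 for ANCOVA. That is a separate matter. It is shown here only because 27 is the size at which the two tests are compared.

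**Precision.** In units of the score variance:
- t-test on change: v = 2(1 − r) = 2 × 0.5 = 1.00
- ANCOVA with the baseline score as covariate: v = 1 − r² = 1 − 0.25 = 0.75

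The ratio is (1 − r²)/[2(1 − r)] = (1 + r)/2 = 0.75, so the t-test loses (1 − r)/2 = 25% of the precision. Its standard error is 1/√0.75 = 1.155 times as large, about 15% more. Put another way, 27 per group under ANCOVA is worth 27/0.75 = 36 per group under the t-test.

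| r | precision lost, (1 − r)/2 |
|---|---|
| 0.3 | 35% |
| 0.5 | 25% |
| 0.7 | 15% |
| 0.8 | 10% |
| 0.9 | 5% |

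**Power at 27 per group, effect 0.4 (noncentral t).**
- t-test on change: noncentrality 0.4/√(2 × 1.00/27) = 1.470, 52 df, power 30.3%
- ANCOVA: noncentrality 0.4/√(2 × 0.75/27) = 1.697, 51 df, power 38.4%

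**False positives (simulated null trials, 27 per group, r = 0.5).**
- t-test on change alone: 4.9%
- ANCOVA alone: 4.9%
- smaller of the two p-values always reported: 7.2%, falling to 6.4% at r = 0.8
- t-test on change, switching to ANCOVA only when the baseline scores differ at p < 0.05: 4.3%

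**Disagreement.** The two tests differ on significance in about 4.5% of null trials and about 16% of trials with a true effect of 0.4.

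**The case against.** The strongest reply is that this is a condensed article about a feasibility trial. Efficacy is secondary, effects are to be read cautiously, and an analysis plan that is not shown may fix the model and the covariate list. The sentence also covers outcome measures in general, not only the cognitive one. Much of this stands. A full covariate list is not owed here, and the point carries modest weight. What remains is that the article does state a rule, that the rule is an open either/or, and that it covers the outcome on which the trial says it is powered.

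Blinding of the statistician also helps. Coded arms hide the direction of the effect, which makes it harder to steer towards a favourable result. They do not hide p-values.

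A reader might infer more than the text supports in three ways:
- **That covariates will be chosen by observed imbalance, and that this inflates error.** The phrase about baseline differences can equally mean adjusting for participants' differing baseline values, the baseline score included. Even on the data-driven reading, switching to ANCOVA on observed imbalance gave 4.3%, below nominal.
- **That the plan gives up a quarter of its precision.** That is so only if the t-test is chosen, r is 0.5, and the alternative is an ANCOVA containing the baseline score, which the article does not clearly promise.
- **That the false-positive rate is 7%.** That is a worst case in which the smaller p-value is always reported. Nothing in the article says this will happen.

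**Conclusion.** The concern holds in a limited form. The article leaves the efficacy test as an unresolved choice and does not clearly place the baseline cognitive score in the model. At r = 0.5 the t-test option costs 25% of the precision available from ANCOVA on the baseline score, or about 30% against 38% power at 27 per group and an effect of 0.4. The loss shrinks to 10% to 15% if r is 0.7 to 0.8. Selective reporting between the two tests could raise the false-positive rate to about 7% at worst.

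These figures assume a two-sided 5% level, equal variances at baseline and endpoint, and normally distributed scores. They ignore any further gain or cost from adding cognitive stage. This is worth correcting but does not threaten the trial's primary feasibility objectives.

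**What to change.** For the cognitive efficacy outcome, name one primary analysis in advance. For example: *The primary efficacy analysis is an ANCOVA of the post-test score on arm, the baseline score of the same measure and cognitive stage at baseline, fitted whatever baseline imbalance is observed, and reported as an adjusted mean difference with 95% confidence interval. A t-test on change is a sensitivity analysis.* State the significance level and sidedness alongside it.

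The cost is one sentence and two degrees of freedom if stage has two levels. No new data are needed, since Table 5 already schedules the cognitive measures at baseline and post-test. Which cognitive measure is primary, and how the exploratory scales are analysed, are separate questions that this change does not settle.
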